# The 6 municipalities will switch from control phase to intervention phase in a randomized order

### Objective

The main aim of the present study is to assess the effectiveness, feasibility, and costs of a tailored strategy to implement the SAMBA model for integrated OA care in primary health care in Norway.

### Hypotheses

A priori, we hypothesize that the tailored strategy for implementing the SAMBA model for integrated OA care in a primary care setting will:Result in higher quality of care than in current OA care (higher compliance with treatment recommendations [2, 6–8] measured by patient-reported achievement of process quality indicators in OA care [20])Result in more GP referrals to FLS/physiotherapy and more discharge reports from FLS/PTs to referring GPs than in current OA careResult in less GP referrals to MRI for participants with OA and less GP referrals to orthopaedic surgeons in secondary care that does not lead to scheduled joint surgeryResult in higher patient satisfaction with the new OA care model than in current OA careBe more effective than current OA care in improving lifestyle changes (e.g. increase the proportion of people with OA that meet the American College of Sports Medicine’s recommendations for physical activity and reduce the proportion of people with OA that are overweight)

## Methods/design

### Study design

In order to implement the model and to assess the effects of the tailored strategy, a stepped wedge cluster randomized controlled trial will be conducted [41]. The GPs and the PTs in the six participating municipalities (clusters) in Øvre Romerike will switch from control (current OA care) to intervention (implementation of the SAMBA model for integrated OA care) phase in a randomized order. All municipalities start the trial simultaneously and act as controls until the point in time they are randomized to crossover from the control to the intervention phase, and all municipalities have implemented the SAMBA model for OA care by the end of the inclusion period (Fig. 1).

**Fig. 1 Fig1:**
[figure not shown]
Timeline for the SAMBA project. *Dark cells represent intervention periods, and blank cells represent control periods. The inclusion of patients will start on January 15^th^ 2015 and end on June 15^th^ 2016. The last six month follow-up will be in December 2016 and the last 12-month follow-up will be in June 2017. ^#^The 6 municipalities will switch from control phase to intervention phase in a randomized order

### Setting

The study will be conducted in six neighbouring municipalities north of Oslo (Eidsvoll, Gjerdrum, Nannestad, Hurdal, Ullensaker, and Nes) in collaboration with the regional hospital (Department of Orthopaedic Surgery at Akershus University Hospital), the Department of General Practice at Oslo University Hospital, and National Advisory Unit on Rehabilitation in Rheumatology at Diakonhjemmet Hospital.

### Randomization and blinding

The municipalities will be randomly allocated to one of the six sequences for time of crossover from control to intervention (implementation) phase using a computer-generated list of random numbers. Since the number of inhabitants in the six municipalities varies, stratification on the number of inhabitants less than versus more than 20,000 will be performed to ensure a mix of municipality sizes in the randomized sequence. The allocation sequence will be provided by a statistician. Due to the nature of the implementation strategy, it is not possible to blind the involved GPs and PTs, but the research coordinator performing the telephone interviews will remain blinded. Statistical analyses of primary and secondary outcomes will be performed by the primary investigator and the statistician blinded for group allocation.

### The control phase

During the control phase, the GPs and the PTs receive no activities to promote the use of the SAMBA model for integrated OA care or any other facilitation towards an uptake of the guideline recommendations for OA treatment. Participants with hip and/or knee OA included during the control phase may receive physical therapy as usual, but not the patient education programme, the OA information booklet, exercise diary, or any of the other ‘activities’ in the SAMBA model for integrated OA care prior to 12 months post-baseline.

#### The GP workshop training package

The principal investigator will be responsible for the GP workshops together with the study coordinator, members of the project group, and two orthopaedic surgeons from the regional hospital, Akershus University Hospital. PT representatives will be invited to attend the GP workshop. The GP workshop will last about 1.5 h and consist of three parts: (1) a summary of international evidence-based recommendations for OA care; (2) an introduction to the SAMBA intervention; (3) a presentation by an orthopaedic surgeon on surgical treatment that is provided, the appropriate time to refer people with OA for assessment of surgical treatment, and what kinds of treatment (non-surgical) or other assessments (conventional radiographs) that should have been provided before a referral. The presentation is followed by a discussion with the GPs regarding the timing and the content of referrals for assessment of surgical treatment.

#### The PT workshop training package

The PTs will attend a 1-day workshop-based education programme as part of the ‘Active life with osteoArthritis’ (ActiveA) programme, which is a Norwegian initiative similar to the Swedish BOA [17] (http/:utv.boaregistret.se) and the Danish GLA:D [18] (http/:glaid.dk). The ActiveA programme has been developed and is currently undertaken as collaboration between researchers at Oslo University Hospital and Diakonhjemmet Hospital, Oslo (see Additional file 3 and www.aktivmedartrose.no).

The PT workshop includes education in delivering OA care in accordance with clinical guidelines in a standardized, evidence-based intervention. Education about healthy nutrition and weight reduction will also be included in the workshop. The PTs will receive a complete patient OA education programme (PowerPoint file) to use in their clinical setting as well as a selection of suggested exercises. Furthermore, the PTs will receive information and instructions regarding the SAMBA model for integrated OA care.

### Recruitment of GPs and PTs

GPs and PTs working in private institutes or at FLSs will be invited during outreach visits to each practice and clinic. We aim to recruit 26 (30 %) of the GPs (currently 80 GPs), all PTs (currently 8) at the six FLSs, and 35 (50 %) of the PTs in private practice (currently 70 PTs). In order to facilitate a high attendance among the GPs, the project group will preferably use one of the regular, established meetings in each municipality for the workshop.

### Recruitment of participants with hip and/or knee OA

Participants will be recruited among individuals that visit their GP with activity-related hip or knee pain/complaints. The GPs will identify eligible people with hip and/or knee OA, hand out a single-paged information sheet about the study, and ask for permission for giving the project group their name and phone number. For those who agree, their name and phone number are then mailed by the GP or their secretary in prepaid envelopes to the project group for further contact. The project coordinators will then provide study information by telephone and perform a screening in relation to the inclusion and exclusion criteria (Table 2). Those that comply with the criteria will receive the written information material and consent form and have 2–3 days to decide if they want to participate in the study.

**Table 2 Tab2:** Criteria for inclusion or exclusion

Inclusion criteria	Exclusion criteria
• Males and females 45 years or older • Activity-related hip and/or knee pain/complaints AND • Clinical signs and symptoms corresponding to hip and/or knee OA OR radiologically diagnosed OA OR registered in the medical journal with the ICPC codes L89 (osteoarthritis of the hip), L90 (osteoarthritis of knee), and/or L91 Osteoarthritis (not classified elsewhere).	• Total hip or knee replacement in the actual joint(s) and no pain/complaints in the other hip or knee joint(s) • Inflammatory rheumatic diseases (e.g. rheumatoid arthritis, spondyloarthritis) • Malignant illness or other major conditions (i.e. unstable cardiovascular disorders or lung disease, dementia) that restrict the ability to adhere to the recommended OA treatment • Do not understand the Norwegian language

A computer programme for identifying eligible people with hip and/or knee OA will be developed. The GP or their secretary may run the programme once a month in order to get a list of patients. This list includes patients that have consulted their GP in the last 30 days and are registered with the following International Classification of Primary Care (ICPC) codes in the past 2 years: L89 (OA of the hip), L90 (OA of the knee), L91 (OA not classified elsewhere), L13 (hip symptoms/complaints), L 15 (knee symptoms/complaints), or L20 (joint symptoms/complaints not classified elsewhere). The programme excludes people registered with ICPC codes L88 (rheumatoid arthritis), T92 (gout), and P70 (dementia). When the GP identify eligible people appearing on this list who were not informed about the SAMBA study during their consultation, a letter will be sent from the GP asking the individuals for permission to be contacted by the study coordinator. Information leaflets and wall posters in the GP waiting rooms as well as newspaper articles and information at local meetings in the Norwegian Rheumatism Association can raise awareness of the study so that the individuals can ask their GP about it. In addition, the PTs at FLS and in private practice will be instructed to ask recently referred people with OA if they have received a request to participate in the SAMBA study.

### Sample size calculations

Previous research in the ‘Musculoskeletal pain in Ullensaker Study’ showed that about 12 % of the adult population self-reported OA in their hip and/or knee joints. Among these, 89 % visited their GPs in the previous year. The estimated adult population (aged 40–70) in the six municipalities in Øvre Romerike is about 35 000, of which about 4200 might have hip and/or knee OA and 3700 might visit their GP during a 1-year period. Based on results from a study in 2012 among 1052 members of the Norwegian Rheumatism Association with hip and/or knee OA, we have estimated the intraclass correlation coefficient (ICC) (using the 19 counties as clusters) to be <0.01. Further, we have estimated that a minimum of 194 individuals in each group among the six clusters with an average of 50 individuals per cluster, achieves 80 % power to detect a 10-unit difference between the group means of the primary outcome measure (OsteoArthritis Quality Indicator questionnaire); when the standard deviation for the primary outcome measure is 24 units, the drop-out rate is 30 %, and the intraclass correlation is 0.01, using a two-sided test with a significance level of 0.05. Hence, we aim to include at least 388 individuals in total.

### The primary outcome measure

The participants with hip and/or knee OA will self-report the primary outcome measure, as well as most secondary outcome measures, at five time points: baseline (shortly after the GP consultation) and then 3-monthly (Table 3). The primary outcome will be patient-reported quality of OA care as measured by the OsteoArthritis Quality Indicator questionnaire, a 17-item questionnaire that includes quality indicators (QIs) related to OA patient education and information, regular provider assessments, referrals, and pharmacological treatment [20]. The items were developed from a literature review of published QIs, expert panels, and patient interviews. The patient self-report questionnaire covers one A4 page with yes/no and ‘not applicable’/‘don’t remember’ as response options, and a previous application has showed acceptable validity and reliability in an OA cohort [20]. The total QI pass rate for each person will be calculated as the total number of QIs they passed, divided by the total number of QIs for which they were eligible. At inclusion, the primary outcome measure may be used to assess the effect of the intervention of the GP consultation, whereas at follow-up, it may be used to assess the total effect of the new model.

**Table 3 Tab3:** Primary and secondary outcomes

	Measurement scale	Time^a^
Primary outcome measure (patient-reported)		
OsteoArthritis Quality Indicator Questionnaire [20]	0–100 % (pass rate)	0, 3, 6, 9,12
Patient-reported secondary outcome measures		
Pain level in hip/knee past week	NRS 0–10	0, 3, 6, 9,12
Stiffness in the hip/knee past week	NRS 0–10	---“---
Hip/knee function in the past week	NRS 0–10	---“---
Patient global assessment of the OA disease	NRS 0–10	---“---
Patient acceptable symptom state (PASS)	Acceptable/unacceptable	---“---
Function (Knee injury and Osteoarthritis Outcome Score OoL subscale [44]/Hip disability and Osteoarthritis Outcome Score OoL subscale [45] (K/HOOS)	4 items, 5-point scale	---“---
Physical activity (frequency, intensity, duration) [47]	3 items	---“---
Daily hours in sitting position	1 item	---“---
Satisfaction with the care provided (from patient experience questionnaires [48])	1 item, 5-point scale	---“---
Health related quality of life (EQ-5D) [49]	5 items, 5-point scale	---“---
Body weight	kg	---“---
Health care use past 3 months		---“---
Patient Specific Functional Scale [43]	NRS 0–10	Pre- and post exercise programme
Adverse events	1 item	Exercise diary
Measured patient secondary outcomes		
30-s chair-stands test [50]	Number of stands	Pre- and post exercise programme
6-min walk test [51]	Metres	---“---
Stairs test [52]	Seconds	---“---
GP- and PT-reported secondary outcome measures		
Knowledge about recommended OA care	2 items, 5-point scale	Pre- and post-workshop + 6 months post-workshop
Attitude towards OA treatment and recommendations	4 items, 5-point scale	---“---
Behaviour in OA care (referrals, imaging)	---“---	---“---
Register based data secondary outcome measures		
Number of referrals to secondary care that does not lead to scheduled joint surgery		0–12
Number of referrals to MRI for OA assessment		---“---
Number of GP referrals for OA patients to PTs at FLSs/private practice		---“---
PTs at FLSs/in private practice secondary outcome measures		
Number of discharge reports from PTs at FLSs/ private practice to the referring GP		0–12

^a^0 = baseline assessment, the other numbers indicate months after baseline assessment

*MRI* magnetic resonance imaging, *NRS* numeric rating scale

### Secondary outcome measures

Secondary outcomes will include both process and effect evaluation measures reported by the participants with OA, the GPs, and the PTs as well as data obtained from registers (Table 3). The number of ‘responders’ in the two groups will be compared using the OMERACT-OARSI responder criteria [42]. A participant will be classified as a responder if one of the following is fulfilled:High improvement in pain or function≥50 % improvement + absolute change of ≥2 in self-reported pain (numeric rating scale (NRS), 0–10), OR≥50 % improvement + absolute change of ≥2 in self-reported function (NRS, 0–10)Improvement in at least two of the three following:≥20 % improvement + absolute change ≥1 in self-reported pain (NRS, 0–10)≥20 % improvement + absolute change ≥1 in patient global assessment of disease activity (NRS, 0–10)≥20 % improvement + absolute change ≥1 in self-reported function (NRS, 0–10)

Only participants recruited during the intervention phase will keep an exercise diary. Their attendance at patient OA education sessions, exercise sessions (group/ individual), healthy eating programme (FLS) as well as use of the number of exercise sessions recorded in the exercise diary will be registered. The 6-min walk test, stair test, and 30-s chair-stand test will be administered by the PTs before and after the treatment period. Test results are registered in the exercise diary by the PT. In collaboration with the PT, the participants fill in the Patient Specific Functional Scale [43] by self-selecting between one and three activities that they are unable to do or have difficulty doing as a result of their OA disease. The level of difficulty for each activity is patient-reported before and after the treatment period in the exercise diary using an 11-point numeric rating scale (0 = unable to perform activity, 10 = able to perform activity at pre-disease level).

GPs’ and PTs’ attendance at the workshops will be registered. The GPs and PTs will respond to a questionnaire immediately before and after the workshop as well as after 6 months. Telephone interviews with estimated 10 % of the involved GPs and PTs will be undertaken 6 months post-workshop regarding whether they have implemented the SAMBA model (i.e. referred to physiotherapy, arranged patient OA education programmes, offered a supervised exercise programme), their experiences with the implementation strategy, and reasons for eventual non-use of the SAMBA model. Also, about 10 participants with hip and/or knee OA will be telephone interviewed regarding their experiences with the SAMBA model for integrated OA care. The interview data will be explored by text analyses, coded, and combined into broad categories.

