**Methods/design:**

A cluster randomized controlled trial with stepped wedge design including an effect, process, and cost evaluation will be conducted in six municipalities (clusters) in Norway. The municipalities will be randomized for time of crossover from current usual care to the implementation of the SAMBA model by a tailored strategy. The tailored strategy includes interactive workshops for general practitioners (GPs) and PTs in primary care covering the SAMBA model for integrated OA care, educational material, educational outreach visits, feedback, and reminder material. Outcomes will be measured at the patient, GP, and PT levels using self-report, semi-structured interviews, and register based data. The primary outcome measure is patient-reported quality of care (OsteoArthritis Quality Indicator questionnaire) at 6-month follow-up. Secondary outcomes include referrals to PT, imaging, and referrals to the orthopaedic surgeon as well as participants’ treatment satisfaction, symptoms, physical activity level, body weight, and self-reported and measured lower limb function. The actual exposure to the tailor made implementation strategy and user experiences will be measured in a process evaluation. In the economic evaluation, the difference in costs of usual OA care and the SAMBA model for integrated OA care will be compared with the difference in health outcomes and reported by the incremental cost-effectiveness ratio (ICER).

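### As stated, adverse events are recorded only in the exercise diary that intervention-phase recruits keep, so harms cannot be compared with usual care

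*Protocol article*

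**What the plan says.** The adverse-event row of Table 3 reads "Adverse events 1 item Exercise diary". The column that gives 0, 3, 6, 9 and 12 months for the questionnaire outcomes gives the diary here instead. The section on secondary outcome measures restricts the diary to one group: "Only participants recruited during the intervention phase will keep an exercise diary". The section on the control phase agrees. Until 12 months after baseline, control recruits may have their usual physiotherapy, "but not the patient education programme, the OA information booklet, exercise diary, or any of the other" components of the SAMBA model.

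The diary also holds the performance tests. On these the protocol says "The 6-min walk test, stair test, and 30-s chair-stand test will be administered by the PTs before and after the treatment period", and then "Test results are registered in the exercise diary by the PT". The Patient Specific Functional Scale is filled in there too. Table 3 ties these measures to the exercise programme and not to months since baseline, for example "Number of stands Pre- and post exercise programme". The abstract lists "self-reported and measured lower limb function" among the secondary outcomes.

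**The concern.** A harm outcome in a controlled trial is informative only if it is sought in the same way in both groups. Here it is sought in one. Control recruits can have physiotherapy as usual, so treatment-related events can occur among them as well, but nothing stated in the article would record them. A count from the intervention group alone cannot show whether the new model adds harm, reduces it or leaves it unchanged.

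The diary may also miss events inside the intervention group. It serves to log exercise sessions and programme tests. A participant who is offered the model but never starts the physiotherapy programme has little reason to fill in a diary, yet belongs to the group under the intention-to-treat principle that the protocol adopts for its primary analysis.

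This is a decision about data collection. A statistical analysis plan cannot repair it afterwards.

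**Working it through.** The plan gives no figure on this point, and its sample size concerns the primary outcome. The check is a trace of each outcome to its source and to the people who supply that source.

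**Step 1: source and coverage** (Table 3; sections on secondary outcome measures and the control phase)

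| Outcome | Source and timing | Control-phase data |
|---|---|---|
| Adverse events, one item | Exercise diary | None stated |
| Chair-stand, walk and stairs tests | Physiotherapist, around the exercise programme, in the diary | None stated |
| Patient Specific Functional Scale | Around the exercise programme, in the diary | None stated |
| NRS pain, function and global assessment; K/HOOS subscale listed under function; EQ-5D; health care use | Questionnaire at 0, 3, 6, 9 and 12 months | Yes |

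**Step 2: search for another route.** The data collection section describes the questionnaires and the telephone screening. The register section covers medication, sick leave, secondary care and joint surgery, subject to permission. The telephone interviews with about 10 participants concern experience with the SAMBA model. None of these names adverse events.

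**Step 3: consequence.** A group contrast needs an event proportion in each group. The control proportion would rest on 0 observations, so the contrast cannot be estimated, whatever the number of control recruits. For scale only: the planned total is 388 in equal groups, 388 / 2 = 194, so about 194 people would be without the item if the planned split were achieved. The actual split depends on recruitment in each period.

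**Step 4: what a change during the trial could still capture.** Inclusion runs from 15 January 2015 to 15 June 2016, and the last 12-month follow-up is in June 2017. The trial status section describes October 2015.

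- The first recruits have questionnaires due in April (3 months), July (6 months) and October 2015 (9 months), and in January 2016 (12 months). By mid-October 2015, three of their four follow-up questionnaires have fallen due.
- All municipalities begin in the control phase, so these earliest recruits are controls.
- Anyone recruited after the change contributes all four follow-up points. By the end of inclusion every municipality has crossed over, so the latest recruits are intervention participants.

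The lost follow-up therefore falls mostly on early control time, and group is tied to calendar time in what remains. The exact crossover dates are in a figure that is not reproduced in the text, so the loss cannot be counted more closely.

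**The case against.** The strongest reply is that the arrangement is disclosed and contradicts nothing. The protocol says that secondary outcomes include both process and effect measures, states openly who keeps the diary, and promises no between-group test of any diary item. Its hypotheses name neither harms nor measured function. This stands. It disposes of one tempting inference, that the trial promises a controlled comparison of measured function which it cannot deliver, or that its evaluation of function is lost. NRS function and the K/HOOS subscale that Table 3 lists under function are collected in everyone at five time points, and NRS function also enters the responder criteria compared between groups. What remains on measured function is a label: the article does not say which secondary outcomes are process measures.

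A second reply is that worsening pain, function, quality of life and health care use are recorded in both groups, with register data to follow if permitted. These are useful indirect signals, so it would be wrong to infer that the trial is blind to harm in controls. They are not defined as adverse events, however, and do not replace a question about them.

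A third reply is that the article is condensed and the full protocol may describe another route. That is possible, so the point is limited to what is stated. But Table 3 does not leave the matter open. It names a source, and that source exists in one group only.

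Finally, the wording of the item is not shown. If it asks about exercise sessions, it cannot be moved unchanged into control questionnaires. This stands and shapes the fix.

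**Conclusion.** The point holds for adverse events. On the stated plan there are no control observations, no comparison of harms with usual care is possible, and events may be missed in intervention participants who never start the programme. The first two statements follow directly from the text. The third is an inference from the purpose of the diary, because the article does not describe how diaries are issued or returned.

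The planned 30% drop-out should not be read as the share of diaries that will be missing. It is an input to the sample size for the primary outcome, and the article gives no diary-return rate. Nor does the text support a prediction that pre-post test changes will be presented as trial effects, since the article makes no such claim.

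The primary outcome and the controlled comparison of function are unaffected. The adverse-event gap is worth correcting because the remedy is cheap and the missing data cannot be reconstructed later. The labelling of the performance tests and the Patient Specific Functional Scale is minor.

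**What to change.** Add a one-item adverse-event question to the remaining 3-, 6-, 9- and 12-month questionnaires for all participants, worded so that it applies to any OA care and not only to exercise sessions. Keep the diary item as an additional record of events during the programme, reported separately.

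Compare the questionnaire item by group with adjustment for calendar period and cluster. If events are too few for that model, give counts and denominators by group and period. Report that follow-up before the change is missing and that most of it is early control follow-up.

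In Table 3, mark the chair-stand, walk and stairs tests and the Patient Specific Functional Scale as within-intervention descriptive measures that carry no effectiveness claim.

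The cost is one extra item on a questionnaire that already goes to everyone, an amendment while data collection is under way, and a footnote. The drawback is an incomplete control record that is unbalanced over time: follow-up before the change cannot be recovered, and the comparison will be weaker than if the item had been asked from the start.
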